### Plans for communicating protocol amendments to relevant parties and trial results to participants

Important protocol modifications such as changes to eligibility criteria, outcomes, or analyses will be notified to relevant parties (e.g., Research Ethics Committee, researchers, participants, and journal of publication). Furthermore, the results of the trial will be presented to the participants by email or in future scientific publications.

### Sample size calculation

The sample size and power calculations were based on the previous study [46]. The calculations were based on detecting a mean difference of 4.21 points on the Neck Disability Index, assuming a standard deviation of 5.58 points, a two-tailed test, an alpha level of 0.05, a desired power of 80% and an estimated 15% dropout rate. These assumptions generated a sample size of a minimum of 32 participants per group.

### Statistical analysis

The data distribution will be determined by visual analysis of histograms. The baseline characteristics of participants will be calculated through descriptive statistics. Potential differences between groups and 95% confidence interval for the 6-week and 3-month follow-ups after randomization will be calculated by using Linear Mixed Models with the interaction between the intervention group and time. Missing data will be handled using linear mixed models (ie, imputation methods were not needed) [47]. An estimation approach will be used to interpret the findings rather than using statistical significance. The principles of intention-to-treat analysis will be used [48] and data analysis will be performed by using the Statistical Package for the Social Sciences (SPSS) version 17.0.

## Discussion

This randomized clinical trial aims to present a protocol to investigate the effect of a telerehabilitation program versus a self-care booklet on pain and functional disability, through a randomized controlled trial designed for patients with chronic nonspecific neck pain. The null hypothesis tested will be that patients allocated in the intervention group present outcomes not significantly different from the control group. In our hypothesis, patients allocated to the intervention group experience outcomes that are similar to those of those assigned to the self-care digital booklet. Our hypothesis can then be approved or disapproved based on the results of the study.

Neck pain is a common musculoskeletal condition that impairs the life quality of millions of people worldwide [49] and is a clinically important condition for physical therapists. This randomized clinical trial will provide reliable information on the use of telerehabilitation to treat patients with chronic non-specific neck pain. It is expected that telerehabilitation of patients with neck pain by using an exercise program will figure as an efficient method.

There is a lack of high-quality research on the effects of telerehabilitation in patients with neck pain and functional disability. Therefore, the outcomes of this study will corroborate the scientific community on the effectiveness of a telerehabilitation protocol in patients with neck pain.

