**Methods:**

This is a prospectively registered, assessor-blinded, two-arm randomized controlled trial comparing a telerehabilitation exercise program versus a digital booklet with self-care information. Seventy patients will be recruited with non-specific chronic neck pain. Follow-ups will be conducted post-treatment, 6 weeks, and 3 months after randomization. The primary outcome will be disability at post-treatment (6 weeks) measured using neck pain disability. Secondary outcomes will be pain intensity levels, global perceived effect, self-efficacy, quality of life, kinesiophobia, and adherence to treatment. In our hypothesis, patients allocated to the intervention group experience outcomes that are similar to those of those assigned to the self-care digital booklet. Our hypothesis can then be approved or disapproved based on the results of the study.

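### The stated hypothesis is that the two arms are similar, but the trial is sized and analysed to look for a difference and gives no margin by which similarity could be judged

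*Protocol article*

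**What the plan says.** All references are to the protocol article.

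- **Research hypothesis.** The Discussion states: "In our hypothesis, patients allocated to the intervention group experience outcomes that are similar to those of those assigned to the self-care digital booklet". The Abstract (Methods) repeats it: "patients allocated to the intervention group experience outcomes that are similar to those of those assigned to the self-care digital booklet". Both places add: "Our hypothesis can then be approved or disapproved based on the results of the study". No criterion for approval is given.
- **Null hypothesis.** The Discussion gives it as: "The null hypothesis tested will be that patients allocated in the intervention group present outcomes not significantly different from the control group".
- **Sample size calculation.** "The calculations were based on detecting a mean difference of 4.21 points on the Neck Disability Index", "assuming a standard deviation of 5.58 points", with "a two-tailed test, an alpha level of 0.05", 80% power and 15% dropout, giving at least 32 per group. The Abstract plans 70 patients, and allocation is 1:1.
- **Statistical analysis.** Between-group differences with 95% confidence intervals come from linear mixed models with a group-by-time interaction. On interpretation: "An estimation approach will be used to interpret the findings rather than using statistical significance".
- **Aim and expectation.** The Introduction sets out to evaluate the effect of the exercise program against the booklet. The Discussion expects telerehabilitation to turn out an efficient method. The exercise group also receives the booklet given to controls.

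No equivalence or non-inferiority margin, and no other rule for calling two outcomes similar, is stated anywhere.

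**The concern.** The research hypothesis and the null hypothesis make the same statement, and nothing is set against them. In a trial built to detect a difference, the null can be rejected or left standing, but leaving it standing does not establish it. Similarity can be shown only by an interval that lies inside a margin fixed beforehand, and there is none.

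At stake is the headline conclusion. The results are to approve or disapprove similarity, with no criterion for either. An interval too wide to tell could therefore be written up as confirming that supervised exercise plus the booklet does no better than the booklet, when a real benefit was simply not resolved.

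**Working it through.** **1. Reproducing the stated sample size.** Inputs from Sample size calculation: difference 4.21, SD 5.58, two-sided alpha 0.05, power 80%, dropout 15%.

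n per arm = 2 × [(1.960 + 0.842) × 5.58 / 4.21]² = 27.6 evaluable. Allowing for dropout, 27.6 / 0.85 = 32.4, which agrees with the stated 32 (33 if rounded up). A one-sided version gives 22 evaluable and 26 after dropout, which does not match. The figure is an ordinary two-sided difference calculation.

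**2. Completers per arm.** From the minimum of 32: 32 × 0.85 = 27.2, taken as 27. From the planned 70 (35 per arm): 35 × 0.85 = 29.75.

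**3. Expected precision at 6 weeks, unadjusted.** Half-width of the 95% interval = t(0.975; 2n − 2) × 5.58 × √(2/n).

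- n = 27: 2.007 × 1.519 = 3.05 points
- n = 29.75: 2.002 × 1.447 = 2.90 points

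An estimate of 2.90 points, on the edge of significance at n = 29.75, has an interval from 0 to about 5.8. That interval contains both no difference and the 4.21 points that the trial is sized to detect, so it could not support similarity.

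**4. How often a non-significant result arises.** Two-sample t-test, non-central t with non-centrality = true difference / [5.58 × √(2/n)]. The true differences of 3.0 and 2.0 are assumptions; 4.21 is the planning value.

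| True difference (NDI points) | n = 27 | n = 29.75 |
|---|---|---|
| 4.21 | 22.3% | 18.4% |
| 3.0 | 50.8% | 46.9% |
| 2.0 | 74.7% | 72.6% |

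These become rates of mistaken approval only if non-significance is taken as approval.

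**5. Could the trial show similarity with a margin?** The document gives no margin, so those below are assumptions. Take 29 completers per arm, SD 5.58 and a true difference of 0.

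| Assumed margin (NDI points) | Power, 95% interval inside margin | Power, two one-sided tests at 0.05 each |
|---|---|---|
| 3.0 | 8% | 30% |
| 4.21 | 61% | 77% |
| 5.0 | 84% | 92% |

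Whether the planned size would serve a similarity aim depends entirely on a margin that has not been set.

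**The case against.** The strongest reply is that the harm needs a rule the protocol does not contain. A reader might infer that a non-significant result would count as approval, and hence that a less informative trial is more likely to have its hypothesis approved. Nowhere does the protocol say so. Statistical analysis reports differences with 95% intervals and sets significance aside as the basis for interpretation. That stands, and it limits the claim to what could happen. It does not remove the problem: the section gives no value against which an interval would show similarity, and the Discussion still frames the null in terms of significance.

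Second, the 18–22% is simply the type II error of a trial planned at about 80% power, and every trial of that design carries it. This stands too. The percentages are conditional on the reading above, on assumed true differences and on an unadjusted comparison. A mixed model that uses baseline NDI could lower them; the document gives no correlation from which to say by how much.

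Third, the similarity sentence may be a clumsy restatement of the null, which it directly follows in the Discussion. The aim, sample size and analysis all fit a difference trial, so a drafting error is plausible. In the Abstract, though, the sentence stands alone as the study's hypothesis, with no null beside it.

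A reader might also infer that the sample size is wrong. It is not: it reproduces for a difference aim, and at an assumed margin of 5.0 points it would even give adequate power for equivalence.

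**Conclusion.** The hypothesis is wrong as written. It asserts similarity, coincides with the null, and cannot be confirmed by a trial sized to detect 4.21 points and analysed for a difference without a margin. The sample size and the planned model are sound for a difference aim and need no change on this account.

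The consequence is a risk to the conclusion, not to the estimate: an imprecise or non-significant result could be presented as confirmed similarity. Were that reading adopted, it would occur in about 18–22% of trials at the planned difference, 47–51% at 3.0 points and 73–75% at 2.0 points. This assumes SD 5.58, 27 to 29.75 completers per arm and an unadjusted t-test.

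The 4.21 points should not be pressed into service as a benchmark for a worthwhile effect or as a margin. The protocol gives it only as the difference to detect, taken from a previous study.

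**What to change.** In the Abstract and the Discussion:

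1. State the null hypothesis as no difference between the arms in mean NDI at 6 weeks, and the alternative as a difference between those means.
2. Delete the sentences that hypothesise similar outcomes and that speak of approving or disapproving the hypothesis.
3. In line with the estimation approach in Statistical analysis, say that the between-group difference will be reported with its 95% interval, that an interval including 0 is not evidence of similarity, and that similarity will be claimed only if the interval lies within a pre-stated and justified margin.

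The cost is a wording change and an amendment note; no further patients or data are needed.

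If the sponsor does intend a similarity trial, steps 1 and 2 do not apply. A justified margin, a decision rule based on the interval and a matching sample-size statement are needed instead. On an assumed margin of 3.0 points, for example, 80% power at a true difference of 0 takes 74 evaluable per arm if the 95% interval must lie inside it (88 after 15% dropout), or 60 per arm with two one-sided tests at 0.05 (71 after dropout).

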## Data Availability

All data will be used only for analysis of the present study and will be protected from any unnecessary exposure. The Consent Form according to the Research Ethics Committee of Universidade Federal do Pará was signed by the authors and patients. The paper information will be kept in binders that will be handled only by the researchers responsible for the study and will be kept in locations that will be accessible only to researchers responsible for data analysis. The online information will be able to the researchers on a personal computer located in the personal room of the researcher responsible for the project. All online information will be assessed just by the responsible researchers of the specific part of the data analysis. All information will be published confidentially, without the name of the subjects exposed. All data will be available for review and confirmation of data analysis when requested by a review process for publication of the article in indexed scientific journals or presentations at the scientific event.

## Abbreviations

SPIRIT: Standard Protocol Items—Recommendations for Interventional Trials
CONSORT: Consolidated Standards of Reporting Trials
DMC: Data Monitoring Committee
